**Figure 1 f1:**
[figure not shown]
Study flow diagram.

**Table 1 T1:** Schedule of recruitment, interventions, and measures.

	Time point (weeks)						
	Baseline		Treatment		Follow-up		
	−4	0	4	8	12	16	20
Enrollment							
Screening	**○**						
Informed consent	**○**						
Previous disease history	**○**						
Medical history of HUA	**○**						
Physical examination	**○**						
Laboratory test for SUA level	**○**	**○**					
**Randomization**		**○**					
Intervention							
Verum acupuncture group		<━━━━━>					
Sham acupuncture group		<━━━━━>					
Lifestyle changes to combat HUA	<━━━━━━━━━━━━━━━━━━━━━━━━>						
Measures							
Change in SUA level			**○**	**○**	**○**	**○**	**○**
Response rate			**○**	**○**	**○**	**○**	**○**
Information on acute gouty arthritis attacks			**○**	**○**	**○**	**○**	**○**
Weight	**○**		**○**	**○**	**○**	**○**	**○**
Intake of acute medication	**○**		**○**	**○**	**○**	**○**	**○**
MASS			**○**	**○**			
AEs			**○**	**○**			
Blinding assessment							**○**

AE, adverse event; HUA, hyperuricemia; MASS, MGH Acupuncture Sensation Scale; SUA, serum uric acid.

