### Randomization and blinding

The Clinical Research Center affiliated to the Tongji Hospital of HUST are responsible for the design of the randomization protocol for this study. After confirmation of eligibility, participants will be randomly allocated to either the verum acupuncture or sham acupuncture group in a 1:1 ratio. Participants will be stratified according to study center, and a permuted block randomization method with a block size of four will be used. The randomization sequences will be computer-generated using a central randomization system and according to the order of participant enrollment. Each research center will have an independent research assistant responsible for generating allocation sequences through a password-protected central randomization system. Acupuncturists will be made aware of group assignments prior to treatment using opaque, sealed envelopes.

As this is a blinded study, participants, outcome assessors, and statisticians will be blinded to treatment assignment. To maintain blinding in participants, acupuncturists will perform a standardized acupuncture ritual across both groups. Because acupuncturists perform acupuncture through the manipulation of needles, the masking of acupuncturists is difficult to achieve.

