### Provisions for post-trial care

All of the interventions we took were harmless to the human body, so we didn't mention Post trial care.

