### Assessment of safety

Adverse events (AEs) in which a causal relationship to the acupuncture cannot be ruled out will be considered an adverse reactions from the acupuncture. AEs related to acupuncture may include abnormal pain, bleeding, congestion, broken needles, bent needles, and dizziness. Any AEs will be recorded by the acupuncturists immediately following each session of acupuncture treatment.

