### Reporting procedures for adverse events

In this study, the acupuncturist will assess acupuncture safety and record acupuncture-related safety data. Details of the acupuncture treatments and AEs arising from the acupuncture will be recorded in the acupuncture record form. If AEs should occur, acupuncturists will promptly take the necessary measures to ensure the patient’s wellbeing. AEs that result in any of the following events will be defined as serious: (1) fatal events, (2) life-threatening events, (3) events that require hospitalization, (4) events that result in severe impairments or disabilities of function, and (5) other clinically significant events or reactions. If any serious AEs occur, the researchers must report them to the principal investigator and the Data and Safety Monitoring Board (DSMB) within 24 hours.

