### Data collection and management

#### Data collection

The investigator will conduct a baseline assessment within 1 month of obtaining informed consent. Demographic and epidemiological data will be obtained using a general information questionnaire, which will record information on age, gender, nationality, education, occupation, weight, height, previous disease history, routine physical examination, and medicine used for hyperuricemia. After receiving health education on hyperuricemia and 1 month of a low-purine diet, the serum uric acid concentrations of patients who have been enrolled in this study will be confirmed by laboratory tests.

During the treatment period, all patients will be asked to rate their acupuncture de qi sensations using the MASS immediately after the end of each acupuncture session. AEs related to acupuncture will be observed by acupuncturists. AEs, such as bent needles, stuck needles, broken needles, fainting, and infections, will be recorded. Serum uric acid concentrations will be tested at 4 and 8 weeks after randomization. During the follow-up period, serum uric acid concentrations will be tested at 12, 16, and 20 weeks after randomization. If patients have gout attacks after randomization, the time and location of the gout attack, and any medication used, will be recorded. All paper-based data will be recorded in the case report form (CRF). The data will be collected up to the time of withdrawal and will be included in the analysis unless participants specifically request for their data to be withdrawn.

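### Non-serious adverse events are judged and recorded by the treating acupuncturist, who knows the arm, and are not scheduled for collection after week 8, so the safety comparison is open to ascertainment bias

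*Protocol article*

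**What the plan says.** Three sections of the protocol article give adverse events to the acupuncturist:

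- Assessment of safety fixes who records and when: "Any AEs will be recorded by the acupuncturists immediately following each session of acupuncture treatment".
- Reporting procedures for adverse events adds the judgement: "the acupuncturist will assess acupuncture safety and record acupuncture-related safety data".
- Data collection, in its paragraph on the treatment period, says "AEs related to acupuncture will be observed by acupuncturists" and gives examples: "AEs, such as bent needles, stuck needles, broken needles, fainting, and infections, will be recorded".

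Randomization and blinding states that "Acupuncturists will be made aware of group assignments prior to treatment using opaque, sealed envelopes" and concedes that "the masking of acupuncturists is difficult to achieve". The same section lists outcome assessors among those who are blinded.

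Table 1 ("Schedule of recruitment, interventions, and measures") marks the AE row at weeks 4 and 8 only. The rows for SUA, response rate, gout attacks, weight and acute medication are marked at weeks 4, 8, 12, 16 and 20.

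Two other routes exist. Under Reporting procedures for adverse events, researchers report any serious AE to the principal investigator and the DSMB within 24 hours, with no end date given. Under Data collection, gout attacks after randomization are recorded with time, location and medication used.

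**The concern.** The Objectives section names safety alongside efficacy, and the Discussion expects the trial to give reliable evidence on both and to support a recommendation. SUA is a laboratory value, so knowledge of the arm has limited influence on its measurement. Noticing a non-serious AE, and deciding whether to attribute it to needling, are judgements. Here they are made by the person who delivered the needling and knows whether the needles penetrated. That person may expect more events from penetrating needles, or may under-record the consequences of their own technique. The statement that outcome assessors are blinded cannot describe the AE record as written.

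Timing adds to this. An infection would not normally show in the minutes after a session, yet that is when recording is fixed. After the sixteenth session no further AE collection is scheduled.

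The wording on scope is also mixed. Assessment of safety speaks of any AE. Reporting procedures for adverse events describes the acupuncture record form as holding events that arise from acupuncture, and the Abstract likewise refers to acupuncture-related events. If the narrower wording governs, an unblinded judgement on cause comes before anything is written down.

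**Working it through.** The plan gives no AE rate and no safety calculation, so there is no figure to reproduce. The check sets the sections side by side and adds one illustration under stated assumptions.

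**Who records.** Assessment of safety, Reporting procedures for adverse events and Data collection agree on the acupuncturist. Randomization and blinding says that acupuncturists learn the allocation before treatment. None of these sections has anyone unaware of allocation ask participants about AEs.

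**When.** Intervention sets 16 sessions, twice weekly over 8 weeks. For 15 of the 16 sessions the acupuncturist sees the participant again at the next session, so an event that began in between can come to light then. The text does not require anyone to ask about it, and after session 16 there is no next session.

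**Until when.** The Table 1 row for the acupuncture sensation scale has the same two marks as the AE row, and both measures are taken after each session. The marks at weeks 4 and 8 therefore most plausibly stand for the treatment period. Study design gives 8 weeks of treatment and 12 of follow-up, 8 + 12 = 20 weeks after randomization. The part without scheduled AE collection is 12/20 = 60% of calendar time. No needling takes place in those 12 weeks, so 60% is not a share of exposure or of events.

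**What is still captured after week 8.** Serious AEs (24-hour reporting, no stated end date), gout attacks and acute medication (both to week 20). What remains without scheduled collection is the non-serious event that is not a gout attack.

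**Illustration of differential recording (assumptions, not figures from the plan).** Let the true AE rate be p in both arms, and let the arms be captured with probabilities s₁ and s₂. Then:

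- recorded risk ratio = (p × s₁)/(p × s₂) = s₁/s₂
- recorded risk difference = p × (s₁ − s₂)

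Set the better-captured arm to 1 and the other to 0.8 or 0.6:

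| True rate p (both arms) | Difference at 1 vs 0.8 | Difference at 1 vs 0.6 |
|---|---|---|
| 5% | 1 point | 2 points |
| 10% | 2 points | 4 points |
| 20% | 4 points | 8 points |

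The recorded risk ratio is 1/0.8 = 1.25 or 1/0.6 = 1.67 if the first arm is the better captured, and 0.8 or 0.6 if it is the other. The true ratio is 1 throughout. The direction depends on which arm is under-recorded, and the document does not settle that.

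**The case against.** The strongest reply is that the acupuncturist is the natural observer of bent, stuck or broken needles and of bleeding, that participants are blinded, and that harm from needling should mostly appear during the 8 weeks in which needling happens. Most of this stands. It justifies keeping the acupuncturist's record for procedural events. It does not justify making it the only described source for non-serious events that need judgement or appear later.

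Several stronger readings are tempting, and the documents do not support them:

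- *The safety comparison is biased.* A reader might infer this from the unblinded recorder. Neither direction nor size follows from the text. It is open to bias, which is a weaker statement.
- *Nothing is captured after the last session, or every AE record comes from an unblinded operator.* The serious-AE route is assigned to the researchers and has no stated end date. The discontinuation criteria mention a serious event during or after treatment, a DSMB monitors safety, and gout attacks are followed to week 20. The serious-AE route is a reporting duty, however, and no one is told to ask participants.
- *Only events thought related to acupuncture are sought.* Assessment of safety says any AE, and counts an event as a reaction when a causal link cannot be excluded. The wording is inconsistent across sections, but it is not uniformly narrow.
- *Between-session events are lost.* They can surface at the next session during the treatment period.
- *60% of the safety information is missing.* The figure is calendar time without needling.
- *The remark "All of the interventions we took were harmless to the human body" shows prejudged recording.* It sits under Provisions for post-trial care and does not govern AE collection.

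It might also be said that the full protocol or an analysis plan could supply the detail. But recorder, timing and the Table 1 marks are rules that the article states, so the point does not rest on silence.

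**Conclusion.** The point holds for non-serious AEs. As written, they are observed, assessed and recorded by a treating acupuncturist who knows the allocation, immediately after each session, with no scheduled collection in the 12 weeks after treatment. The between-arm safety comparison is therefore open to ascertainment bias of unknown direction and size, and late non-serious, non-gout events may go unrecorded.

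The illustrative risk ratios of 0.6 to 0.8 or 1.25 to 1.67 rest wholly on the assumed relative capture of 60% to 80% and equal true rates. They show what such a gap would do and do not predict what will happen. The primary endpoint, its analysis and the sample size are untouched. The change is worth making because a stated objective depends on it and the cost is low.

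**What to change.** 1. Extend the AE row of Table 1 to weeks 12, 16 and 20.
2. At each scheduled visit from week 4 to week 20, have existing staff who are unaware of allocation ask one standard open question on all AEs since the last visit, whatever the suspected cause. The research assistant who generates the allocation sequence at each center should not be the one who asks.
3. Keep the acupuncturist's form for in-session procedural events.
4. Make Assessment of safety, Reporting procedures for adverse events and Data collection consistent that all AEs are recorded.

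The cost is a protocol amendment, a line on the CRF and a few more unrelated events to code. Contact already exists: SUA is measured at these time points, and the Discussion has participants submit a lifestyle questionnaire to research assistants every 4 weeks. The article does not say which staff meet participants at each visit, so the sponsor must confirm that someone unaware of allocation is available.

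Two limits should be acknowledged. Needle sites differ by arm (abdomen and legs against the back, Table 2), so an answer that names a site can reveal the arm; the standard question protects the asking more than the later judgement. Recruitment began in July 2022 and data collection is under way, so participants enrolled before the change will have less complete AE data than those enrolled after it. The report should say so and show AEs separately for the two periods.

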### Baseline psychological outcome measures

To test the effects of neuropsychological factors on acupuncture, the 60-item Neuroticism-Extraversion-Openness-Five Factor Inventory (NEO-FFI) short-form test, the Acupuncture Expectancy Scale, the Beck Anxiety Inventory (BAI), the Beck Depression Inventory II (BDI- II), the Patient–Doctor Relationship Questionnaire (PDRQ-9), and the Difficult Doctor–Patient Relationship Questionnaire (DDPRQ-10) will be evaluated once at baseline.

### Reporting procedures for adverse events

In this study, the acupuncturist will assess acupuncture safety and record acupuncture-related safety data. Details of the acupuncture treatments and AEs arising from the acupuncture will be recorded in the acupuncture record form. If AEs should occur, acupuncturists will promptly take the necessary measures to ensure the patient’s wellbeing. AEs that result in any of the following events will be defined as serious: (1) fatal events, (2) life-threatening events, (3) events that require hospitalization, (4) events that result in severe impairments or disabilities of function, and (5) other clinically significant events or reactions. If any serious AEs occur, the researchers must report them to the principal investigator and the Data and Safety Monitoring Board (DSMB) within 24 hours.

### Data collection and management

#### Data collection

The investigator will conduct a baseline assessment within 1 month of obtaining informed consent. Demographic and epidemiological data will be obtained using a general information questionnaire, which will record information on age, gender, nationality, education, occupation, weight, height, previous disease history, routine physical examination, and medicine used for hyperuricemia. After receiving health education on hyperuricemia and 1 month of a low-purine diet, the serum uric acid concentrations of patients who have been enrolled in this study will be confirmed by laboratory tests.

During the treatment period, all patients will be asked to rate their acupuncture de qi sensations using the MASS immediately after the end of each acupuncture session. AEs related to acupuncture will be observed by acupuncturists. AEs, such as bent needles, stuck needles, broken needles, fainting, and infections, will be recorded. Serum uric acid concentrations will be tested at 4 and 8 weeks after randomization. During the follow-up period, serum uric acid concentrations will be tested at 12, 16, and 20 weeks after randomization. If patients have gout attacks after randomization, the time and location of the gout attack, and any medication used, will be recorded. All paper-based data will be recorded in the case report form (CRF). The data will be collected up to the time of withdrawal and will be included in the analysis unless participants specifically request for their data to be withdrawn.

#### Electronic data management

Data will be managed using the electronic data capture (EDC) system hosted at the Data Management Center of Tongji Hospital. Database builders will create electronic CRFs (eCRFs) using the CRFs and all annotations on the CRF. All collected data from the CRF will be entered into the EDC system twice by two independent investigators to ensure the accuracy of the data. After all data are checked, the database will be locked. Any modifications after the database is locked will be discussed by the principal investigator and sighed by the data entrant. Both the paper and electronic documents will be held for at least 5 years after publication.

#### Monitoring and quality control

The trial protocol was formulated by experts in the fields of acupuncture, rheumatology, statistics, and public health. When a revision is needed, an amended protocol will be resubmitted to the Clinical Trial Ethics Committee of Tongji Medical College, HUST, for review. To guarantee the quality of the study, we will provide a standardized training course to all research centers before recruitment, which includes the methods for screening patients, acupuncture delivery, data collection, data input, and an introduction to the database. After initiation, the trial will be monitored regularly by inspectors from the Tongji Hospital, Tongji Medical College, HUST. A Data and Safety Monitoring Board (DSMB) has been set up to monitor the performance and safety of the trial, which is composed of five experts from different fields based on the Chinese mainland. Any modifications to the data can be traced in the Beijing Absolute Clinical Data System electronic data capture (AbsEDC) platform. The reasons and details for drop-outs or withdrawals will be documented.

#### Sample size

The primary efficacy end point of this trial is the reduction in SUA from baseline at 8 weeks after randomization. The sample size of this study is driven by the superiority test of the primary efficacy endpoint, aiming to demonstrate a greater reduction in SUA concentration in the verum acupuncture group compared to the sham acupuncture group. Based on the pilot study and a previous clinical trial (33), we anticipate that SUA concentration will be reduced by an average of 0.58 mg/dL ± 1.15 mg/dL more in the verum acupuncture group than in the sham acupuncture group. Therefore, a sample size of 142 participants (71 patients in each group) is required to detect the difference between study groups with 85% power at an alpha level of 0.025 (one-sided). Considering an expected attrition rate of 20%, we plan to enroll at least 180 participants into this study.

#### Statistical analysis

Statistical analyses will be performed using SAS (SAS Institute, v.9.4) by an independent statistician who is blinded to group allocation. Efficacy analyses will be performed primarily on the full analysis set (FAS). A sensitivity analysis will be performed on the per-protocol set (PPS) if deemed necessary.

The primary end point will be summarized descriptively, and the hypothesis will be tested based on the analysis of covariance (ANCOVA) model with the intervention group as the main effect and baseline SUA and study center as covariables.

For other end points, continuous data yielding normal distributions will be summarized using means and standard deviations. Differences between the two groups will be tested using Student’s *t*-test. For results with non-normal distributions, data will be expressed using medians and quartiles, and comparisons between the two groups will be performed using the Mann–Whitney *U* test. Categorical end points will be summarized in terms of frequencies and percentages, and comparisons between the two groups will be performed using the Pearson *χ*² test or Fisher’s exact test, as appropriate. The statistical test for the primary end point will be at the one-sided 0.025 alpha level. Unless otherwise specified, all other end points will be tested at the two-sided 0.05 alpha level.

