### Inclusion criteria

Meets the diagnostic criteria for hyperuricemia, in accordance with the guidelines of the American College of Rheumatology (2012) (37).Aged 18–65 years (regardless of sex),SUA ≥ 7–11.0 mg/dL after 1 month of a low-purine diet,No history of gouty arthritis.Has not received uric acid-lowering drug treatment or stopped uric acid-lowering drug treatment ≥ 12 weeks before randomization.18.5kg/m^2^ ≤ body mass index (BMI) ≤ 30.0 kg/m^2^.Written informed consent.

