## Outcomes

### Primary outcome

Participants’ SUA levels will be evaluated at six time points during the study: once at baseline (week 0), twice during the treatment period (4 and 8 weeks post randomization), and three times during the follow-up period (12, 16, and 20 weeks post randomization). The primary end point of this study is the reduction in SUA level from baseline to 8 weeks after randomization.

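### Free improvement, not an error: the valid primary ANCOVA could also adjust for the week -4 SUA that Table 1 already schedules

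*Protocol article*

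**What the plan says.** - **Scheduled measurements.** In Table 1, the row "Laboratory test for SUA level" in the enrollment block is marked at week -4 and at week 0. Both precede treatment.
- **Entry gate.** Inclusion criteria require "SUA ≥ 7–11.0 mg/dL after 1 month of a low-purine diet". Data collection says that after the diet month "the serum uric acid concentrations of patients who have been enrolled in this study will be confirmed by laboratory tests". Under the Table 1 schedule that is the week-0 test.
- **Baseline.** Primary outcome counts six SUA time points and takes the pre-treatment one "once at baseline (week 0"). Week -4 is not among the six.
- **Endpoint.** "The primary end point of this study is the reduction in SUA level from baseline to 8 weeks after randomization".
- **Model.** Statistical analysis specifies ANCOVA "with the intervention group as the main effect and baseline SUA and study center as covariables".
- **Planning figures.** Sample size assumes that SUA is "reduced by an average of 0.58 mg/dL ± 1.15 mg/dL more in the verum acupuncture group" than in the sham group, and asks for 71 per group "with 85% power at an alpha level of 0.025 (one-sided").

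**The concern.** One week-0 reading does two jobs: it admits the patient, and it is the only SUA value in the model. A second pre-randomization reading on the same patient carries further information about that patient's usual level. If it helps to predict week-8 SUA beyond what week 0 already tells, leaving it out makes the standard error of the verum–sham difference larger than the scheduled data allow. What is at stake is precision, not validity.

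There is a side issue. Patients admitted on a high reading tend to read lower next time, treated or not. The fall from baseline within each arm will therefore contain some regression to the mean. The secondary threshold of SUA ≤ 7.0 mg/dL is exposed as well, because it sits at the lower entry limit.

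**Working it through.** **1. The plan's own figure.** Inputs from Sample size: difference 0.58, SD 1.15, one-sided alpha 0.025, power 85%.

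n per arm = 2 × (1.960 + 1.036)² × 1.15² / 0.58² = 2 × 8.978 × 1.3225 / 0.3364 = 70.6, so 71 per arm and 142 in total. With 20% attrition, 142 / 0.80 = 177.5, so 178, which the protocol rounds up to 180. The stated size reproduces, with power 85.2% at 71 per arm by the normal approximation.

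**2. Gain from a second baseline, equal correlations.** Let r be the correlation between any two SUA values in a patient and s² their variance. The protocol does not give r, so it is assumed.

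- One baseline: residual variance = s²(1 − r²)
- Two baselines: residual variance = s²(1 − 2r²/(1 + r))
- Ratio = (1 + 2r)/(1 + r)²

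| r | ratio | cut |
|---|---|---|
| 0.3 | 1.6/1.69 = 0.947 | 5% |
| 0.5 | 2.0/2.25 = 0.889 | 11% |
| 0.7 | 2.4/2.89 = 0.830 | 17% |
| 0.8 | 2.6/3.24 = 0.802 | 20% |

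Simulation with entry gated at 7–11 mg/dL on week 0 gives the same ratios. The gate on week 0 does not by itself create the loss.

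**3. When the gain shrinks.** Let q be the correlation of week -4 with week 8, and keep r for the other two pairs. Then R² = (q² + r² − 2qr²)/(1 − r²).

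- r = 0.5, q = 0.4: R² = (0.16 + 0.25 − 0.20)/0.75 = 0.28. Ratio = 0.72/0.75 = 0.96, a cut of 4%.
- First-order autoregressive pattern, q = r²: R² = r², so the ratio is 1 and there is no gain.

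**4. One worked case.** Assumed: usual SUA mean 7.8 mg/dL, between-person SD 1.0, within-person SD 0.9. After gating on week 0, the SD of change is 1.19, close to the planned 1.15.

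- Total variance = 1.00 + 0.81 = 1.81; r = 1/1.81 = 0.552
- One baseline: 1.81 × (1 − 0.305) = 1.258
- Two baselines: 1.81 × (1 − 0.610/1.552) = 1.098, a cut of about 13%
- Power = Φ(0.58/√(2 × variance/71) − 1.96). One baseline: Φ(3.081 − 1.96) = 87%. Two baselines: Φ(3.298 − 1.96) = 91%.

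If week -4 SUA also had to be at least 7 mg/dL, simulation puts the cut at about 7–9%: the upper end with no variation in response to the diet, the lower end with a diet-response SD of 0.4.

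**5. Power with 1.15 read as the SD of change.** Here s² = 1.15²/(2(1 − r)). With 71 per arm, power goes from 93.5% to 95.7% at r = 0.5, and from 90.3% to 94.7% at r = 0.7. The one-baseline model already exceeds 85% in both.

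**6. Regression to the mean within an arm.** With no treatment or diet effect, expected fall = (1 − r) × (mean at entry − ungated mean). Assume a level SD of 1.15 and an ungated mean of 6.5 to 8.0 mg/dL; the simulated mean at entry is then 7.76 to 8.37.

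- r = 0.5: from 0.5 × (7.76 − 6.5) = 0.63 down to 0.19 mg/dL
- r = 0.7: from 0.3 × (7.76 − 6.5) = 0.38 down to 0.11 mg/dL

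Under the same assumptions, about 11–45% of an untreated arm would be at or below 7.0 mg/dL at week 8. The step 4 inputs give a fall of 0.26 mg/dL. In all cases the expected difference between arms is zero.

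**The case against.** The strongest reply is that nothing here is wrong. ANCOVA on the protocol-defined baseline and the stratification factor is a standard, valid model, and omitting an optional covariate neither biases nor contradicts anything. That stands, and it is why this is only an improvement.

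The reply also holds that the week -4 test is a screening test taken before the diet month, so the post-diet value is the natural baseline. Its place in the enrollment block does point to screening, although no section says so. This is a good reason to keep week 0 as the baseline and not to average the two values. It is no reason to ignore week -4 as a separate covariate.

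Finally, the gain rests on correlations that nobody has stated, and it can vanish. That stands too; the range has to start at zero.

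Two stronger readings are tempting. A reader might infer that the trial loses needed power. The protocol's own figures do not support this, since the one-baseline model already exceeds 85% in the cases examined. A reader might also infer that regression to the mean inflates the primary result. It does not: both randomized arms pass the same gate, the test compares arms, and no within-arm test is planned. The Discussion remark about bringing SUA into an optimal range is conditional and is not a decision rule. Nor would the extra covariate change the raw within-arm falls, so the two matters should be kept apart.

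**Conclusion.** The point holds as an optional gain in efficiency. The primary model is sound but uses one of two scheduled pre-randomization SUA values. Using both would cut residual variance by roughly 0–15%, reaching about 20% only if SUA values are highly and equally correlated (r near 0.8). At r = 0.5 to 0.7 with equal correlations, this is worth about 2 to 4 points of power. These sizes assume normality and correlations that the protocol does not report, and they lie at the lower end if week -4 was also gated or predicts week 8 less well than week 0 does.

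Regression to the mean is a caution for reporting only. It could reach the size of the assumed 0.58 mg/dL effect within an arm under the widest assumptions, yet it contributes nothing in expectation to the difference between arms.

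**What to change.** Before unblinding, add week -4 SUA to the primary ANCOVA as a separate second covariate, next to group, week-0 SUA and center. Do not average the two values, because week -4 precedes the diet month and the average would mix two conditions. Leave the endpoint and its week-0 baseline unchanged.

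Where within-arm reductions and per-arm rates of SUA ≤ 7.0 mg/dL are reported, add a sentence saying that week 0 was the qualifying value and that only the adjusted verum–sham difference is interpreted as a treatment effect.

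The cost is one model term, one degree of freedom and one sentence. No new data, visits or patients are needed. Recruitment is already under way, so the change should be dated and documented; if added after unblinding it would look post hoc.
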